### ***2.4 Protecting against sources of bias.***

It will not be possible to blind study participants to study arm allocation due to the nature of the intervention. This should not introduce a significant risk of bias as the outcome measures are highly standardized. To minimize risk of bias, the research associate conducting the photographic analysis (i.e. degree of contamination) will be blinded to study arm allocation.

## **2.5 Inclusion and exclusion criteria.**

Participants from inpatient units, intensive care units, operating room units and emergency departments across all sites will be recruited. Inclusion criteria for the airway provider include: (1) Attending physician or fellow in emergency medicine, intensive care, pediatrics, or anesthesia; and (2) Adult or Pediatric Advanced Life Support certification. Inclusion criteria for the airway assistant include: (1) Attending physician, resident, fellow, nurse or respiratory therapist; and (2) Adult or Pediatric Advanced Life Support certification. Exclusion criteria: (1) Decline to provide informed consent; or (2) Unable to perform tasks required of the role due to physical limitations.

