### 1.2 Principal research questions.

The primary aim of this study is to evaluate the effectiveness of aerosol box use, compared with no aerosol box use, for reducing HCP contamination during performance of AGMPs by a trained airway team during care of a simulated patients in respiratory failure due to COVID-19. We hypothesize that the use of an aerosol box, compared with no aerosol box use, will reduce HCP contamination caused by AGMPs during care of simulated patients in respiratory failure due to COVID-19.

The secondary aim is to determine if aerosol box use influences the time to successful completion and first-pass success rate for ETI and LMA insertion in trained airway teams. We hypothesize that there will be no significant differences in time to ETI and LMA insertion and first pass success rates when comparing airways teams using an aerosol box with teams not using an aerosol box.

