## 2.2 Trial interventions.

The aerosol box is a transparent, plastic cube covering the patient’s head and shoulders, with circular access ports on the front of the box allowing for access to manage the airway (see budget). An additional four access holes (i.e. two on either side of the box) allow for airway assistants to access the patient airway (Figure 3). As our study includes only one airway assistant, the two holes that are not in use will be sealed shut during the study. The airway assistant will be directed to stand in a standardized position, to the immediate right of the airway provider. In a prior study, an aerosol box placed over the head of an adult volunteer demonstrated air leaks out of the box during exhalation and coughing that could be eliminated with the addition of a plastic drape. For this reason, we have incorporated a plastic drape extending from the top of the box down to the patient’s chest to prevent spread of aerosols. In another experiment, the addition of continuous wall suction to the aerosol box setup resulted in significantly decreased airborne particle exposure (for the airway provider) compared to aerosol box use without suction. Given that wall suction is readily available and accessible in most acute care areas, our aerosol box setup will include wall suction, with suction tubing running into the aerosol box at one point along the bottom of the box near the head of the patient. Wall suction will be set at 200 mmHg, which is consistent with the pressure used in prior studies and measured in the engineering lab of [name] (co-applicant) to generate a negative airflow of approximately 50 L/min.

All participants (i.e. airway provider and airway assistant) randomized to the intervention arm will receive aerosol box training. A short video will orient them to the design of the aerosol box and include expert-modeled demonstration of strategies for optimal BVM ventilation, ETI, and LMA insertion using an aerosol box with a 2-person airway team. The training video will be shot in English and French to permit viewing across study sites in Alberta, Ontario and Quebec. After viewing the video, participants will work in pairs to practice all three procedures for a maximum of 15 minutes, providing them opportunity to coordinate their movements to optimize efficiency. After each procedure, they will receive feedback from a local airway and aerosol box expert (i.e. site investigator).

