### **2.16, 2.17 *Statistical analysis.***

Demographic characteristics of participants including sex, profession, years of clinical experience and other identifiers (e.g. height, body surface area) will be reported using descriptive statistics between 2 study arms. For the primary outcome, assuming non-normal distribution of data, we will use Wilcoxon rank sum tests to compare the AOC in 3 different procedures in both airway providers and assistant roles. Analyses to evaluate the degree of contamination pre- and post-doffing of PPE will be conducted separately. Time to procedural completion and first pass success rates will be compared with the Wilcoxon rank sum tests.

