### **2.18 *Subgroup analysis.***

Although stratifying by sex during randomization will ensure equal distribution of different sex in both groups, the physical stature of each provider may be a factor that influences the extent of contamination. We will conduct secondary analysis to explore if factors other than aerosol box (i.e. sex, body surface area, number of years clinical experience of the airway expert, experience of doing multiple procedures within incubator) will influence the degree of contamination, time to successful intubation and LMA insertion, and first pass success rate for ETI and LMA insertion using mixed-effect linear regression model. The similar secondary analyses focusing on the degree of contamination of the airway assistant will be performed as well while stratified by these factors.

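### Provider specialty is neither a stratification factor nor a listed model factor, so the unadjusted comparison of time and first-pass success gives up precision that an item already known from eligibility could recover

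*Protocol*

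**What the plan says.** The secondary aim in Protocol 1.2 is a comparison of arms: "The secondary aim is to determine if aerosol box use influences the time to successful completion and first-pass success rate for ETI and LMA insertion". The same section states the expectation that the arms will not differ significantly on these outcomes.

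Five provisions bear on how precisely that comparison can be made:

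- **Eligibility (2.5).** The airway provider qualifies by: "1) Attending physician or fellow in emergency medicine, intensive care, pediatrics, or anesthesia; and (2) Adult or Pediatric Advanced Life Support certification". The airway assistant qualifies by: "1) Attending physician, resident, fellow, nurse or respiratory therapist; and (2) Adult or Pediatric Advanced Life Support certification". Recruitment covers inpatient wards as well as intensive care, operating rooms and emergency departments. Neither role needs prior experience of the procedures.
- **Randomization (2.3).** Teams are stratified by site and by sex of the airway provider, in blocks of 4.
- **Main comparison (2.16, 2.17).** Time and first-pass success are compared by Wilcoxon rank sum tests, with no covariate or stratum. Background data are described by arm: "Demographic characteristics of participants including sex, profession, years of clinical experience and other identifiers".
- **Secondary model (2.18).** A mixed-effect linear model explores factors other than the box. They are sex, body surface area, "number of years clinical experience of the airway expert" and experience of procedures inside an incubator. Specialty is not listed.
- **Sample size (2.10).** It rests on the primary outcome alone. No SD for time and no success rate is given.

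**The concern.** Time to place a tube or LMA, and success at the first attempt, depend on who is holding the device. Section 2.5 allows an attending anesthesiologist and a ward pediatrician to serve in the same role. If these groups differ in speed, that difference enters the error variance of an unadjusted comparison and can also fall unevenly between arms by chance. Years of clinical experience is a weak stand-in: a pediatrician long in practice may score higher than an anesthesia fellow while intubating far less often.

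The stake is a missed effect. When the stated expectation is no significant difference, extra noise makes the data more likely to agree with it whether or not the box slows the procedure. Protocol 1.1 intends to weigh these times and success rates against contamination to inform practice and policy, so a missed slowing would carry weight.

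**Working it through.** **1. The plan's own figure.** Inputs from 2.10: d = 0.65, significance level 0.05 (taken as two-sided), power 0.8, three scenarios per team, intra-cluster correlation 0.7.

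- One measure per team: 2 × ((1.960 + 0.842)/0.65)² = 37.15 per arm.
- Mean of three correlated measures: variance factor (1 + 2 × 0.7)/3 = 0.80.
- 37.15 × 0.80 = 29.7, that is, 30 teams per arm.

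The stated 30 is reproduced, but for the primary outcome averaged over three scenarios.

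**2. One procedure at 30 per arm.** Time to intubation, or to LMA insertion, is a single measure per team. By normal theory the detectable difference at 80% power is 2.802 × √(2/30) = 0.72 SD. Let f be the share of total variance due to skill. An effect of 0.65 within-skill SD (0.65 is borrowed from 2.10 only as a yardstick) becomes 0.65 × √(1 − f) in total SD:

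| f | Unadjusted power |
|---|---|
| 0 | 0.71 |
| 0.20 | 0.62 |
| 0.40 | 0.50 |
| 0.60 | 0.36 |

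**3. An illustration in seconds.** Assumed, since the documents give nothing: skilled providers 30 s (SD 10), others 60 s (SD 20), 25% others.

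- Total variance: 0.75 × 100 + 0.25 × 400 + 0.75 × 0.25 × 30² = 343.75, SD 18.5 s.
- Within-group variance: 75 + 100 = 175, SD 13.2 s.
- Skill share: 168.75/343.75 = 0.49.

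Simulated power for a 10 s slowing at 30 per arm, two-sided 0.05, with skill group known exactly, is about 0.70 for the planned Wilcoxon test, 0.83 for a linear model adjusted for skill group, and 0.90 for a skill-stratified Wilcoxon test.

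I repeated this with normal times, each provider drawn independently into a group, 6,000 trials per setting and stratum weights 1/(stratum size + 1):

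| Share of others | Planned Wilcoxon | Adjusted linear model | Stratified Wilcoxon |
|---|---|---|---|
| 10% | 0.87 | 0.92 | 0.94 |
| 25% | 0.69 | 0.82 | 0.89 |
| 40% | 0.53 | 0.71 | 0.81 |

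The 25% row agrees with the figures above within simulation error.

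**4. When the marker is imperfect.** I then placed 10%, 20% or 30% of providers in the wrong group at random, keeping 25% others and a 10 s slowing. The stratified Wilcoxon test had power 0.81, 0.76 and 0.71, and the linear model 0.67, 0.61 and 0.57, against about 0.70 for the planned test. So the gain shrinks as the marker worsens, and a linear model on raw times can lose to the planned rank test.

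**5. Bias.** With no box effect and 25% others, the planned test rejected in 4.9% of trials. A separate simulation with a skewed two-group mix gave 4.6%. Under unstratified 30 v 30 allocation, an imbalance of 6 or more providers (20 points) in a skill group has probability 0.10 at 25% prevalence and 0.16 at 50%.

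**6. First-pass success.** At 30 per arm, control rates of 95, 90, 80 and 70% need box-arm rates of about 67, 59, 45 and 34% or lower for 80% power. This outcome can show only very large losses, so precision is scarce here too.

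**The case against.** **Randomization already deals with skill.** A reader might infer that operator skill distorts or swamps the box effect. The documents do not support that. Teams are randomized, the type I error stays near 0.05, and chance imbalance is already allowed for in that error rate. The loss is one of precision, and without an SD for time its size is unknown.

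**The aim and the criteria contradict each other.** The aim concerns effects on "influences the time to successful completion and first-pass success rate for ETI and LMA insertion in trained airway teams", and 2.18 speaks of an airway expert, so a reader might conclude that the sample cannot answer the question. But Protocol 1.1 contrasts trained two-person teams with a box study whose participants had very brief training and no assistant. Trained can therefore mean box-trained pairs. Section 2.2 supplies that training to the arm that uses the box: participants "randomized to the intervention arm will receive aerosol box training", and "participants will work in pairs to practice all three procedures for a maximum of 15 minutes". No aim claims expert intubators, and the expert label appears once.

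**Experience is already in the model.** This stands in part. Years of experience is not the only skill-related factor, because incubator experience is also listed and bears on working through access ports. It is still not general airway skill.

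**Normal theory makes the loss look larger.** With d = 0.736 at 30 per arm, a t-test calculation on the assumed mixture gives a detectable slowing of 0.736 × 18.5 = 13.6 s. The plan states a Wilcoxon test, which a slow tail affects less: its power at 13.6 s is about 0.90. The penalty is smaller than the t-test suggests, but it remains.

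**Broad eligibility is a legitimate choice, and covariates may belong in the SAP.** The first part stands: restricting providers would cost generalisability. On the second, an SAP may exist that is not shown. But the protocol itself names the test and the list of factors, and specialty is missing from both.

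**Conclusion.** The point holds as a loss of precision on the secondary outcomes. Section 2.5 admits four specialties with no airway-experience requirement, while specialty is absent from the strata, from the main comparison of time and first-pass success, and from the 2.18 factors.

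Under the assumed 75/25 mix, power for a 10 s slowing is about 0.70 as planned and 0.83 to 0.90 with skill group accounted for. This is an upper bound on what specialty can deliver, since it marks skill imperfectly. The times, SDs and proportions are assumptions: with few less-skilled providers the loss is small, and with many it is substantial.

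The documents do not show bias, a failure to answer the stated question, or any defect in the primary outcome's sample size, which is reproduced. The change is worth making because the expected result is no significant difference and the information is already in hand.

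**What to change.** In Protocol 2.18, add the airway provider's specialty to the listed factors alongside years of clinical experience, which need not be dropped. Group it to avoid sparse cells, for example anesthesia, intensive care and emergency medicine together versus pediatrics, and fix the grouping before arm comparisons are seen.

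Adding a factor to an exploratory model does not alter the main comparison. So also state in 2.16, 2.17 that the arm effect on time and first-pass success will be reported adjusted for or stratified by this grouping. For time, a specialty-stratified Wilcoxon test stays closest to the planned method and, in the check above, tolerated an imperfect marker better than a linear model on raw times. For first-pass success, a stratified comparison such as Mantel-Haenszel would serve.

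Leave the eligibility criteria unchanged.

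The cost is slightly more analysis work. No new data are needed, because specialty is checked at eligibility. If first-pass failures are few, some cells may be sparse even after grouping, and the gain for that outcome may be slight.

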## **2.6, 2.7 Duration of treatment period and frequency of follow up.**

Individual recruitment sessions will be run over the course of the same day. There are no planned follow up sessions.

## **2.8, 2.9 Outcome measures.**

Primary outcome: Surface area of contamination (AOC) quantified from digital photos of GloGerm™ deposited on the airway team members pre and post-doffing. A digital reference grid will be applied over each photo, with mean grey values of areas within each grid “pixel” calculated using Image J (NIH) software. As areas highlighted by GloGerm™ will illuminate more brightly, mean grey value per pixel will be the base unit to quantify degree of contamination relative to the provider’s anatomic surface area. This quantitative measure permits comparative analysis between groups or scenarios, and is congruent with accepted measures in the bioimaging informatics, digital immunohistochemistry, and direct immunofluorescence. Digital images of participants will be captured in a standardized fashion under UV-illumination in a fashion to minimize confounders (brightness, angle, lighting) (see budget). Images will be taken pre- and post-doffing to capture extent of contamination on PPE (pre) and extent of contamination on provider surfaces underneath PPE.

Secondary outcomes: (a) time to successful intubation or LMA insertion (captured by video review by 2 trained and calibrated raters); (b) first pass success rate for ETI and LMA insertion (captured by video review by 2 trained and calibrated raters).

## **2.10 Sample size.**

Sample size estimation is based on primary outcome measure. Given the paucity of quantitative research in this area, we propose a sample of 60 teams (120 participants) in total, or 30 teams (60 participants) per study arm. As each team will receive repeated measures (i.e. 3 scenarios), this sample size allows us to detect a medium effect size (Cohen’s  $d = 0.65$ ), with a significance level of 0.05, a power of 0.8, and a high intra-cluster correlation coefficient ( $\rho = 0.7$ ) to make a conservative estimation. Accounting for missing data due to technical issues, we will recruit 2 extra teams per study group, resulting in a total sample size of 64 teams (128 participants).

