### ***2.3 Randomization method.***

Randomization will occur at the level of the team, stratified by study site and sex of the airway provider (to ensure equal distribution of sex in both arms), and conducted in blocks of 4 to ensure an even distribution of teams across study arms. Randomization packages will be prepared at a central study site using a web-based random number generator. Sequentially numbered recruitment packages provided for each site will contain sealed opaque envelopes (i.e. one envelope per study arm) with study arm assignments and unique identifier codes for participants.

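### The 80% power in section 2.10 belongs to one comparison of team means over three scenarios, not to the per-procedure rank-sum tests planned in section 2.16

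*Protocol*

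**What the plan says.** Section 2.10 of the protocol sets the size of the trial: "we propose a sample of 60 teams (120 participants) in total, or 30 teams (60 participants) per study arm". It names the three scenarios as the reason why this number is enough ("As each team will receive repeated measures (i.e. 3 scenarios), this sample size allows us to detect a medium effect size"), gives the effect as Cohen's d = 0.65, and works "with a significance level of 0.05, a power of 0.8" and "a high intra-cluster correlation coefficient ( $\rho = 0.7$ ) to make a conservative estimation". Two further teams per arm are added for missing data, which makes 32 per arm.

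Section 2.16, 2.17 gives the primary analysis: "we will use Wilcoxon rank sum tests to compare the AOC in 3 different procedures in both airway providers and assistant roles". It expects the data to be non-normal, and it analyses contamination before and after doffing separately. It describes no average over scenarios, no repeated-measures model and no other test that combines the three scenarios. The only mixed model in the protocol is in section 2.18, for the secondary analysis of other factors.

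**The concern.** The power statement and the primary analysis appear to describe two different tests. A gain from repeated measures arises only when the three values of a team enter the same comparison. A rank-sum test within one procedure uses one value per team, so the correlation between scenarios plays no part in it.

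If so, the trial states a 20% risk of missing its target effect, and that figure does not belong to any test named for the primary outcome. A non-significant result for one procedure would then be read against a power that was never calculated for it.

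**Working it through.** **Inputs.** From section 2.10: n = 30 teams per arm (32 after the allowance for missing data), d = 0.65, significance level 0.05, power 0.80, m = 3 scenarios, ρ = 0.7. From section 2.3: team-level randomization in blocks of 4, taken as 1:1. Assumptions, because the protocol does not state them: the test is two-sided, d is in units of the single-scenario SD, and the effect is the same in each scenario.

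**Step 1. Reproduce the protocol's figure.** Average the three scenarios within each team.

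- Variance factor: (1 + (m − 1)ρ)/m = (1 + 2 × 0.7)/3 = 0.80.
- Teams per arm: 2 × 0.80 × (1.960 + 0.842)² / 0.65² = 29.7, so 30.
- Detectable effect: 2.802 × √(2 × 0.80/30) = 0.647.
- Power: Φ(0.65 × √(30/1.6) − 1.960) = Φ(0.855) = 0.804 (noncentral t: 0.790).

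This uses every input that section 2.10 states and returns exactly its sample size. The basis of the 80% is therefore one two-sided comparison of team means over three scenarios.

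**Step 2. Apply the same inputs to one procedure.** With m = 1 the variance factor is 1, and ρ drops out.

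- Normal approximation: Φ(0.65 × √(30/2) − 1.960) = Φ(0.557) = 0.711.
- The rank-sum rows below use the asymptotic relative efficiency of the rank-sum test for normal data, 3/π = 0.955. The effective n is 30 × 0.955 = 28.6 per arm, entered in the noncentral t calculation.

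| Test on one procedure, normal data, d = 0.65 | 30 per arm | 32 per arm |
|---|---|---|
| t test (noncentral t) | 69.7% | 72.6% |
| Rank-sum (efficiency 0.955) | 67.6% | 70.5% |
| Rank-sum (simulation, 20,000 data sets) | 67.1% | 70.2% |

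**Step 3. Effect detectable with 80% power on one procedure, 30 per arm.**

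- Normal approximation: 2.802 × √(2/30) = 0.723.
- t test: 0.736.
- Rank-sum: 0.736/√0.955 = 0.753.

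To keep d = 0.65 at 80% power per procedure would take 38 teams per arm (normal approximation), 39 (t test) or about 40 (rank-sum).

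**Step 4. Dependence on the distribution.** Section 2.16 expects non-normal data, so the single-procedure rank-sum test was also simulated with a shift of 0.65 SD, 30 per arm, two-sided 5%. The shapes are assumptions, since the protocol gives no distribution for the area of contamination.

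| Assumed shape | Rank-sum power |
|---|---|
| Normal | about 67% |
| Gamma, shape 2 | 82% |
| Lognormal, σ = 0.5 | 84% to 85% |
| Exponential | 91% |

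Many tied or zero values, which are plausible after doffing, could lower power; they were not simulated.

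**The case against.** The strongest objection concerns the distribution. The 68% is a normal-data figure, and section 2.16 chooses the rank-sum test because it expects non-normal data. With a skewed outcome and a location shift, the same test can exceed 80% at d = 0.65. This stands. A reader might infer that every primary test is underpowered, or that no reading of section 2.16 reaches 80%; the protocol does not support that. It does not make the two sections agree, however. Section 2.10 works in Cohen's d with repeated measures and ρ, and it makes no appeal to skewness.

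Four further objections carry less weight.

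- **Wording.** Section 2.16 uses the word for separate analyses only of the two doffing stages, not of the procedures. That is true, and the primary aim in section 1.2 is one overall question. But an ordinary rank-sum test takes one independent value per team, and no averaging is described, so one test per procedure and role is the natural reading. A reader might instead infer that all three values per team are pooled into one test as if independent, which would inflate the type I error. Nothing in the protocol says so.
- **Sidedness.** A one-sided 5% test on one procedure would have about 81% power by the normal approximation. That calculation ignores the three scenarios and the correlation that section 2.10 invokes.
- **Any-procedure success.** With normal data and correlation 0.7, at least one of the three procedures would be significant in about 84% of trials. Section 2.10 does not claim power in that sense, and the protocol sets no rule for success across procedures. The shortfall is per test only.
- **A separate analysis plan may combine the scenarios.** It may. But the protocol itself fixes both the power basis and the test, and they differ.

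**Conclusion.** The mismatch stands. The stated 80% at d = 0.65 is sound arithmetic for one two-sided comparison of team means over three scenarios, and it does not apply to the rank-sum tests named for the primary outcome.

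If the data are approximately normal, d is in single-scenario SD units and tests are two-sided at 5% without adjustment for multiplicity, the chance of missing the target effect in a given procedure is about 32% by rank-sum with 30 teams per arm, against the stated 20%. It is nearer 27% to 30% if all 32 teams are evaluable. Under skewed data the shortfall may shrink or vanish. What is established is that the stated power is unsupported for the planned tests, not that it is certainly too low. The separate rank-sum tests also remain valid comparisons between arms: this mismatch concerns their power and leaves the type I error of each test as it is.

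**What to change.** **Preferred.** Make the primary test match the calculation. Take one value per team, the mean area of contamination over the three scenarios, and compare it once between arms. A mixed model with arm and scenario as fixed effects and team as a random effect does the same work. Report the per-procedure tests as secondary. The text should also say which role and which doffing stage the primary value refers to, or how they are combined. If the single comparison is itself a rank-sum test, its power under normal data is about 77% with 30 teams per arm and about 80% with 32, so section 2.10 should quote the figure for the test chosen.

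**Alternative.** Keep the separate tests as primary and restate section 2.10 per test: about 68% power at d = 0.65, or 80% power at d of about 0.75, for a rank-sum test with 30 teams per arm, expressly assuming normal data.

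**Cost.** Wording in sections 2.10 and 2.16, with no additional teams. The preferred change has one small downside: procedure-specific results become secondary.
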